## Abstract

**Background:**

TB and HIV form a deadly synergy in much of the developing world, especially Africa. Interventions to reduce the impact of these diseases at community level are urgently needed. This paper presents the design of a community randomised trial to evaluate the impact of two complex interventions on the prevalence of tuberculosis (TB) in high HIV prevalence settings in Zambia and South Africa.

**Methods:**

The interaction between TB and HIV is reviewed and possible interventions that could reduce the prevalence of TB in HIV-endemic populations are discussed. Two of these interventions are described in detail and the design of a 2 × 2 factorial community randomised trial to test these interventions is presented. The limitations and challenges of the design are identified and discussed.

**Conclusion:**

There is an urgent need to reduce the prevalence of TB in communities highly affected by HIV. Potential interventions are complex and require innovative trial designs to provide the rigorous evidence needed to inform health policy makers and to ensure that resources are used optimally.

**Trial Registration:**

Number: ISRCTN36729271

## Background

Tuberculosis (TB) incidence is increasing in much of sub-Saharan Africa, largely due to the high prevalence of HIV infection. International TB control strategies rely on self-presentation of cases to the health services, diagnosis by sputum smear microscopy and the use of a 6–8 month course of multi-drug therapy to cure the disease[1]. However these strategies are currently failing to control TB in high HIV prevalence settings, due both to the massive burden of disease and the inadequacy of existing health systems to find and cure infectious cases coupled with the continuing stigma and denial that surround HIV and TB[2].

The Zambia/South Africa TB and AIDS Reduction (ZAMSTAR) study aims to use existing tools for diagnosis and treatment but to test new approaches to the delivery of TB control strategies to determine whether these can reduce the prevalence of TB and HIV at community level.

### Rationale for ZAMSTAR

The first mechanism by which prevalence of TB could be reduced is through more efficient detection and treatment of infectious cases of TB. Prior to the HIV epidemic, a large body of work provided the backbone for the DOTS strategy, which uses passive case-finding to detect TB cases[3]. Recent work highlights the importance of case-finding and the need to adapt the existing approach to incorporate a more aggressive form of case-detection. The challenge in poorly-resourced settings is how to achieve this without overburdening an already overstretched health service. Sustainable case-finding will need to involve collaboration between the formal health services, other government sectors, community based organisations and the community.

Reducing the reactivation of latent TB infection by preventive therapy and improving the immune function of HIV-infected individuals is another mechanism that could reduce TB prevalence. Randomised trials in developing countries have demonstrated the efficacy of isoniazid in preventing TB in HIV-positive subjects at the individual level[4], but its population-level effectiveness as a TB control measure in HIV prevalent settings has not been proven. Feasibility studies have demonstrated that the main barriers to the successful implementation of this intervention are the difficulties in excluding active TB and low adherence to the course of treatment[5]. For the intervention to be effective at community level, uptake must be increased. Uptake is currently hampered by lack of knowledge of HIV status and poor access to counselling, testing and care as well as by poverty and rural deprivation. TB preventive therapy is also recommended for the household contacts of cases of infectious TB but in most countries is not implemented due to the low priority given to this intervention, lack of available health workers and limited availability of drugs.

HIV infection is widely acknowledged as the driving force behind the current TB epidemic in Southern Africa. Long term control of TB must include addressing the problem of HIV prevention. Proven interventions to reduce the incidence of HIV at a community level are disappointingly few. Provision of voluntary counselling and testing (VCT) has been promoted as an important step in supporting individuals to change behaviour by facilitating knowledge of HIV status. Few trials have used HIV incidence as an end point, although a recent study in Harare among factory workers showed that despite good uptake of VCT HIV incidence was not reduced[6]. Other studies have shown some evidence of behaviour change in HIV-positive individuals but little change has been seen in HIV-negative ones[7]. VCT has been shown to be most effective when offered to couples, since this allows discordant couples to make realistic plans to reduce the risk of HIV transmission[8,9]. Antiretroviral drugs are rapidly becoming more available in developing countries and it is hoped that the increased availability of these drugs may increase uptake of HIV testing and counselling and also reduce transmission of HIV by reducing viral load. This theory is unproven, however, and in wealthier countries, already using antiretrovirals, there is evidence that sexual behaviour has become more, rather than less, risky since their use became widespread and that HIV incidence may be increasing[10].

Finally, stigma is recognised as a barrier for individuals to access diagnosis and care for both TB and HIV. Studies have demonstrated that stigma prevents people (including TB patients or suspects) from: accessing health care, learning their HIV status, disclosing their HIV status to partners, changing unsafe behaviour, and caring for people living with HIV/AIDS (PLWHA), and that the most extreme forms of stigma are often found in households and health facilities [11].

ZAMSTAR has addressed these issues by developing two interventions that combine all of the above strategies and that can be applied at community level. These interventions are community-based enhanced case finding for tuberculosis (ECF) and household counselling and provision of combined TB/HIV prevention services at the household level (HH). The effectiveness of these interventions at population level will be evaluated through a community-randomised trial with a 2 × 2 factorial design.

### Design

#### Study setting

The study is being conducted in Zambia and South Africa, two countries highly affected by the TB and HIV epidemics, and forms part of the CREATE consortium . Study communities have been selected based on TB notification rates greater than 400/100,000 per annum, high HIV seroprevalence and proximity to a TB diagnostic centre. The communities selected are in five provinces of Zambia and in Western Cape province of South Africa and include both urban and rural communities (Fig 1).

**Figure 1 F1:**
[figure not shown]
Map of ZAMSTAR communities.

#### Design of the interventions

##### Enhanced case finding intervention (ECF)

Three components of ECF are being employed at the community and health centre levels.

##### Open laboratory access at health centre

Individuals are able to directly access sputum smear examination for TB at the health centre laboratories, without having to see a clinician or be referred for this service. This service is available continuously and is widely advertised in the community.

##### Community mobilisation and mobile sputum collection points

Community mobilisation is conducted to educate the community about TB and its diagnosis. Mobile sputum collection points are set up at strategic points in the community where symptomatic members of the public are asked to submit sputum samples on the spot and to return the following day for the results. The location of these sputum collection points ensure that all members of the community have access to sputum examination within 30 minutes walk of their home at least three times per year.

##### School mobilisation campaign

All schools in the community receive an annual education programme about HIV and TB. Children are encouraged to take messages about the transmission and diagnosis of TB home so that family members who have been coughing for more than three weeks can submit sputum samples at collection points set up in the schools or at the clinic.

Any cases of TB found by the ECF activities are treated via the routine clinic-based DOTS services.

### Household intervention (HH)

All TB cases diagnosed and notified through the TB control programme are invited to participate in this intervention. All households of TB patients receive information about HIV and TB within the home from a specially trained counsellor. The household members are encouraged to be tested for HIV and screened for TB. A "shared confidentiality" is encouraged between household members to facilitate open discussion of the outcome of the investigations. The household is also encouraged to take responsibility for the member diagnosed with TB and to supervise and encourage treatment compliance. Household members with HIV who do not have active tuberculosis diagnosed are offered TB preventive therapy, as are all children under the age of 6 years, in keeping with national policies (although these are otherwise poorly implemented). Adherence is supported within the family, as well as by the routine treatment support service of the district. All HIV-positive household members will be encouraged to obtain HIV care including antiretroviral therapy (ART) which is provided by the health centres or district hospitals in all of the communities.

### Standard TB/HIV control practice

In all arms of the study, standard TB control practices are supported and, where necessary, improved such that all diagnostic centres are applying a model DOTS programme. Integration of TB and HIV services will be facilitated including diagnostic counselling and testing for HIV in TB patients, referral networks to enable TB patients to access HIV care, screening of HIV positive individuals for TB and the provision of isoniazid preventive therapy for eligible individuals[12].

### Design of the randomised trial

The interventions are being evaluated by means of a 2 × 2 factorial community randomised trial.

The primary study questions are:

• Does enhanced tuberculosis case finding (ECF), by a strategy of community mobilisation and enhanced access to sputum microscopy, reduce prevalence of tuberculosis in the community?

• Does a strategy of combined TB/HIV activities at the household level (HH), that includes active case-finding, isoniazid preventive therapy, and psychosocial and adherence support for both treatment and prevention of tuberculosis and HIV, reduce prevalence of tuberculosis in the community?

The unit of randomisation will be the population accessing one TB diagnostic centre (which will be known as the "community"). A 2 × 2 factorial design will be used so that there will be four arms:

Arm 1: Standard TB/HIV Control activities at the clinic only

Arm 2: Standard TB/HIV Control activities at the clinic *plus *ECF

Arm 3: Standard TB/HIV Control activities at the clinic *plus *HH

Arm 4: Standard TB/HIV Control activities at the clinic *plus *ECF *plus *HH

The primary analysis will be a comparison of ECF Vs no ECF (arms 2 & 4 vs arms 1 & 3) and of HH Vs no HH (arms 3 & 4 vs arms 1 & 2). This allows the questions posed in the specific objectives to be addressed. The factorial design will also allow arm 4 to be compared directly to arm 1, referred to as the control arm in this paper, to address the question:

• What is the overall effect of the combined interventions (ECF+HH) on the prevalence of tuberculosis in the community?

A cohort of consecutive TB patients and their households in each community will be followed for the duration of the interventions to allow analysis of household-level outcomes, using both epidemiological and social science methods.

### Outcome measures

The primary outcome for the study is the prevalence of tuberculosis after three years of intervention, measured through surveys of a random sample of adults (aged > 15 years) from each community.

Secondary outcomes at community level are:

• Incidence of tuberculosis infection measured by repeat tuberculin skin testing (TST) in primary school children found to be TST negative at baseline.

• Tuberculosis treatment outcomes (Cure, Completed treatment, Failed, Defaulted, Died, Transferred) measured by cohort analysis of strengthened tuberculosis register data.

• Additional tuberculosis cases detected by ECF and HH measured using the strengthened laboratory register.

• Uptake of HIV testing and counselling and uptake of and adherence to tuberculosis preventive therapy measured using the testing and counselling register.

• Costs of each component of the intervention and cost-effectiveness comparisons of strategies to find and prevent cases of tuberculosis and HIV.

Secondary outcomes at household level, as measured on a cohort of households are:

• Cumulative HIV incidence measured by serial HIV testing among those over 15 years old.

• Uptake of HIV testing and counselling and uptake and adherence to tuberculosis preventive therapy among household members of TB patients

• Tuberculosis transmission within the household measured by TST and Quantiferon-Gold IT conversion rates

• Cumulative incidence of tuberculosis disease in household contacts

• Stigma levels measured using a quantitative stigma score

### Outcome measurement

#### Baseline assessment of communities

In order to stratify and restrict the randomisation of communities a baseline assessment was conducted by collating information on TB notification rates, TB treatment outcomes, HIV prevalence data and the prevalence of tuberculous infection in school children (see below). In addition to the quantitative baseline assessment, a rapid qualitative appraisal of the communities was conducted. This appraisal involved community mapping, observation and key informant interviews to understand the domains of TB in the local community including population movement, congregation points, beliefs and knowledge about TB and HIV as well as general socio-economic information about the communities

#### Tuberculin Skin Testing

Baseline measurement of tuberculous infection in all ZAMSTAR communities was estimated by means of tuberculin skin testing (TST) surveys among primary school children[13]. These community-wide surveys served three objectives: to characterise ZAMSTAR communities, with regards to TB infection, in relative terms; to inform the randomisation of the communities into the four intervention arms; and to provide data for one of the community-wide secondary outcomes. The design as well as results from these surveys will be described in a separate paper.

The 22,000 children involved in these surveys are being followed up for the three years of the intervention and will be retested at the end of the study to measure the incidence of TB infection in those who were uninfected at baseline.

#### TB prevalence surveys

The primary outcome of the study will be measured by conducting TB prevalence surveys on 5000 randomly selected members of each community. The methodology to be used for these surveys will involve TB culture of 1 respiratory specimen from each adult. The prevalence of TB will be measured as the proportion of these samples that grow *Mycobacterium tuberculosis *using a standard liquid culture technique (MGIT, Becton Dickinson).

#### Secondary outcome cohort (SOC)

150 consecutive TB patients and their households are being recruited in each community and asked to complete a baseline questionnaire containing demographic and specific TB and HIV data as well as questions about stigma relating to TB and HIV. Adults are asked to provide a serum sample to test for HIV and both adults and children are tested for TB infection. This cohort will be visited after eighteen months and again after three years of the intervention to allow measurement of HIV incidence, the incidence of TB infection, the incidence of TB disease and changes in perceptions of stigma.

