### Analytic plan

As a community randomised trial ZAMSTAR will be analysed both at the cluster level, by deriving summary statistics for each community, and at the individual level using data from each individual in each community. For these analyses statistical methods that take account of between- and within-cluster variation will be used. The analysis will give each community equal weight. There are three intervention comparisons that will be made assessing the effects of ECF alone (12 Vs 12 communities), HH alone (12 Vs 12 communities) and ECF plus HH combined (6 Vs 6 communities). Impact measures of the above comparisons will be based on ratios.

To account for the study design, suitable generalized linear models will be used, where appropriate, to allow for clustering by community. For the binary outcomes (prevalence, incidence) the overall risk/rate for each cluster will be calculated. Risks/rates for each cluster will be shown, by strata and arm. A log transformation to normalise data will be applied to the risk/rate for each cluster. The mean and SD of these log risks/rates will be used to obtain the geometric mean (if the log transformation is clearly inappropriate the arithmetic mean will be used instead) and associated 95% CI for each intervention arm of the study. Linear regression of the log mean risk/rate on strata and arm will be used to estimate the relative risk/rate and 95% CI associated with the intervention. The approximate variance for the mean risks/rates ratio is obtained based on the residual mean square from a two-way analysis of variance (ANOVA) of community log-risk on stratum and study arm. A 95% CI for the relative risk/rate will be calculated from this variance using a t-statistic with 16 degrees of freedom (df) for the two main comparisons and 10 df for the comparison of arm 4 Vs arm 1.

For the continuous outcomes such as intervention costs and stigma levels, the overall mean for each community will be calculated, and means for each community will be shown, by strata and arm. The arithmetic mean and SD of these mean scores/numbers and associated 95% CI for each intervention arm of the study will be calculated. Linear regression of the mean score/number on strata and arm (2-way ANOVA on intervention and strata) will be used to estimate the difference in score/number and 95% CI associated with the intervention.

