## Discussion

ZAMSTAR is a trial of two complex public health interventions to assess whether either or both can reduce the prevalence of TB in high HIV prevalence settings. To test such complex interventions, especially when the disease targeted is infectious, requires the use of a community-randomised design. We anticipate that the interventions will act at the individual, household and community levels by finding more cases of tuberculosis more quickly and that this will firstly reduce transmission of tuberculosis in the household and the community and ultimately the prevalence of infection and disease. To enable us to capture all of these steps in the process requires that we also measure the outcomes for individuals, households and communities. We hope that by addressing the two diseases, TB and HIV, together we will also have an impact on HIV. We anticipate that our interventions will allow more individuals to learn their HIV status and to either protect themselves from acquiring HIV or to access necessary HIV care. We do not believe, however, that these interventions will be able to significantly reduce HIV incidence or prevalence at the community level but do hope to be able to show a reduction in incidence at the household level.

To increase trial efficiency, clusters in community randomised trials should be numerous and small[19]. In the context of the ZAMSTAR trial, however, we needed to balance this requirement with knowledge about the transmission of tuberculosis within populations. We believe that to measure effects on transmission and prevalence requires the use of large clusters that encompass entire and discrete populations, so that we can be fairly confident that any case of incident TB was caused by transmission from someone else in that community who had access to the intervention. Due to the necessity to embed the interventions within the existing health services, this dictated that we use the entire population attending one health centre as our community. Consequently although we only have 24 communities, they have a combined population of approximately 1.2 million. A 2 × 2 factorial design allows us to evaluate the two interventions at the same time, thus maximising the cost-efficiency of conducting such a large trial.

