Contamination of a community by a neighbouring community with a different set of interventions was a concern and so the communities needed to be geographically and culturally distinct. Mobility into and out of the communities may also dilute the effect of the interventions and we tried to avoid communities that had high levels of mobility and are using census and qualitative studies to measure the degree of mobility. Additionally we needed to use communities that had high baseline levels of disease to allow us to measure the impact of the interventions, but we wished to maintain a range of urban and rural communities to retain generalisability. Combining these requirements has resulted in widely-spaced communities, using seven different languages and with many different cultures. Health and other infrastructures in these communities are generally poor, generating logistical challenges to conducting the study. Gaining community trust is a process that requires perseverance and understanding on the part of both researchers and community members. Without trust there will not be widespread community involvement in the study, which is necessary to ensure that the interventions work well.

As well as the logistical and field work challenges raised by such a study, there are statistical and design challenges. While the factorial design is cost-efficient, allowing us to evaluate the impact of two interventions in one trial [20], the primary analysis will be based on comparisons of the 12 communities with an intervention vs the 12 without this intervention. We are also powered to measure the combined effect of the two interventions compared with the control arm [arm 1 with arm 4], but not to compare the interventions with each other. A specific consideration in the analysis of factorial trials is the effect of interaction between the interventions and whether this can be accurately measured[21]. It is possible that the ECF intervention will have a larger effect on the primary outcome when combined with the HH intervention, and similarly the HH intervention will be applied to more households if more cases of TB are found using ECF. We do not believe that there will be a significant negative interaction between the two interventions and consider that both interventions will have independent effects. We acknowledge, however, that we will have limited power to detect interactions between the interventions.

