The small sample size also affected our choice of randomisation strategies. Stratification and restricted randomisation were necessary to ensure balance between the arms of the trial and to reduce the between-community coefficient of variation[22].

Despite these challenges the study is underway and the interventions appear to be feasible and popular. One of the study's strengths is that it is embedded within the existing health services, working closely with district and provincial health teams and with clinic staff. The variety of cultures and infrastructure ensures that the results will be generalisable and we can already see that the interventions could be applied in the routine health setting. The primary outcome of the study, TB prevalence, will not be measured until 2010, but already important knowledge is being generated that is helping us understand the complex epidemiology of the TB/HIV epidemic. The results of this trial will provide much needed evidence for health policy makers as they strive to control TB and HIV.

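### Household-cohort index patients are diagnosed after allocation, apparently while ECF is running, so the ECF and arm 4 v arm 1 contrasts on household outcomes are not fully protected by randomisation

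*Protocol article*

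**What the plan says.** The section Secondary outcome cohort (SOC) sets the entry rule: "150 consecutive TB patients and their households are being recruited in each community". Design of the randomised trial repeats it: "A cohort of consecutive TB patients and their households in each community will be followed for the duration of the interventions". Under Outcome measures, this cohort supplies HIV incidence, uptake of HIV testing and of preventive therapy, household TB transmission (conversion on the skin test or Quantiferon), TB disease in contacts, and stigma.

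The ECF section describes the intervention as already in use: "Three components of ECF are being employed at the community and health centre levels". It offers smear testing without referral, mobile collection points and school collection points. The patients it finds join the ordinary treatment stream: "Any cases of TB found by the ECF activities are treated via the routine clinic-based DOTS services". The Discussion expects the interventions to work "by finding more cases of tuberculosis more quickly", and Outcome measures lists extra cases found by ECF and HH as an outcome. On timing, the Discussion says: "Despite these challenges the study is underway and the interventions appear to be feasible and popular".

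The Analytic plan states: "There are three intervention comparisons that will be made assessing the effects of ECF alone (12 Vs 12 communities), HH alone (12 Vs 12 communities", plus the combined comparison at 6 v 6. It makes no exception for household outcomes. It names stigma as an outcome to be analysed this way, and Outcome measures lists stigma only for the household cohort, so the three comparisons do reach this cohort.

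**The concern.** Randomisation balances the communities. It does not balance a sample whose membership is settled later by an event that one of the interventions is built to alter. Here that event is a TB diagnosis. In arms 2 and 4 some of the 150 consecutive patients may be people who would not otherwise have been diagnosed in that period, and their households may differ in background risk, care-seeking or attitudes. A difference between ECF and non-ECF arms in household infection, TB disease, HIV incidence, uptake or stigma could then reflect which households were enrolled and be reported as an effect of ECF, or of ECF plus HH.

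The Discussion comes close to this when it notes that "the HH intervention will be applied to more households if more cases of TB are found using ECF". It treats the link only as a possible interaction between the interventions and does not carry it over to cohort entry.

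**Working it through.** **1. The plan's own figure.** The only figure tied to this cohort is 80% power for a 40% reduction in cumulative HIV incidence (Sample size). Inputs: 12 v 12 communities; p0 = 2.1%, p1 = 0.6 × 2.1% = 1.26%; m = 150 × (2 to 3 adults) × 0.8 = 240 to 360. Power = Φ(√[(12 − 1)(p0 − p1)²/V] − 1.96), with V = p0(1 − p0)/m + p1(1 − p1)/m + k²(p0² + p1²). No k is given for this outcome. Carrying over k = 0.20 gives 59%, 67% and 74% for 2, 2.5 and 3 adults. Using 12 in place of 12 − 1, 3 adults with k = 0.15 gives 81%. The 80% can be neither confirmed nor refuted as stated, and the present point does not depend on it.

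**2. Could recruitment overlap with ECF?** 1.2 million people / 24 communities = 50,000 on average (Discussion). At the selection floor of 400 per 100,000 a year (Study setting) that is 200 notified cases a year. Filling 150 places takes 150/200 × 12 = 9 months, or less where notification is higher. That is long enough to overlap with ECF if the two ran together.

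**3. Apparent ratio when ECF truly does nothing.** Let f be the share of ECF-arm cohort households that enter only because of ECF, and r their outcome risk relative to the rest. Neither is in the documents; both are assumptions. Then

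apparent RR = 1 − f + f·r.

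Two-sided rejection (normal approximation, 12 v 12): d = (p1 − p0)/√(V/12), rejection = Φ(d − 1.96) + Φ(−d − 1.96). Take the HIV outcome with p0 = 2.1%, m = 150 × 2.5 × 0.8 = 300 and k = 0.20 (assumed).

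Example, f = 0.3 and r = 0.5: RR = 0.85 and p1 = 1.785%. V = 0.0000685 + 0.0000584 + 0.0000304 = 0.0001574, √(V/12) = 0.00362, d = −0.00315/0.00362 = −0.87, rejection = 14%.

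| f | r = 0.5 | r = 1 | r = 2 |
|---|---|---|---|
| 0.2 | RR 0.90, 9% | RR 1.00, 5% | RR 1.20, 18% |
| 0.3 | RR 0.85, 14% | RR 1.00, 5% | RR 1.30, 33% |
| 0.5 | RR 0.75, 32% | RR 1.00, 5% | RR 1.50, 67% |

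For a commoner outcome (15% conversion, assumed), f = 0.3 gives 36% rejection at r = 0.5 and 77% at r = 2.

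**4. Which contrasts are exposed?** Write A1 to A4 for the mean log risks by arm, and suppose selection adds log s in arms 2 and 4.
- ECF: ½(A2 + A4) − ½(A1 + A3) is shifted by log s.
- Arm 4 v arm 1: A4 − A1 is shifted by log s.
- HH: ½(A3 + A4) − ½(A1 + A2) is shifted by ½ log s − ½ log s = 0.

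The HH contrast also equals ½[(A3 − A1) + (A4 − A2)]. With 6 communities per arm and equal weights, the planned 12 v 12 comparison already gives the point estimate that pooling within ECF level would give. The cancellation assumes that the shift is the same with and without HH.

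**5. Outcomes outside the cohort.** The prevalence survey samples community members at random, and the school tuberculin cohort was tested at baseline to inform randomisation. Neither sample depends on a TB diagnosis.

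**The case against.** - **Timing is inferred.** The article gives no start dates, and tense is a weak guide: one section speaks of randomisation in the future, another reports it as done. Follow-up for the duration of the interventions, visits at eighteen months and three years, and a count of HIV-negative adults at the start of the study all suggest entry near launch, when ECF has had less time to change the intake. This stands. The point is conditional on overlap, and it disappears where recruitment closed before ECF began.
- **Part of the difference is the intended effect.** The Discussion expects faster detection to reduce transmission within households. For patients who would have presented anyway, a shorter infectious period and less household transmission are real benefits of ECF. This stands; only households that enter because of ECF raise a composition problem.
- **Baseline testing and adjustment help.** Infection is counted as conversion after a baseline test, so much of what was acquired before diagnosis does not count. The Analytic plan also adjusts for baseline factors that differ between arms. Both may reduce the bias, but neither names route or timing of detection, and neither makes the selected households the same.
- **Labelling could be left to the analysis plan.** That is fair for detail. But the article itself states both the entry rule and the three comparisons, without exception.

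A reader might infer that ECF decides which households enter, that the comparison is certainly biased, or that the bias must look like a benefit. The documents support none of these. ECF shifts part of the intake at most, and nothing in the text fixes the sign of r − 1 for any household outcome.

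**Conclusion.** The point holds as a conditional weakness of two secondary contrasts. If cohort recruitment overlapped with ECF, then ECF v no ECF and arm 4 v arm 1 on household-cohort outcomes are not fully protected by randomisation. The bias is zero if households that enter only because of ECF carry the same risk as the others, and can go either way otherwise. Over the assumed ranges (f from 0.2 to 0.5, r from 0.5 to 2) a null ECF would show a ratio between 0.75 and 1.50; these figures illustrate the mechanism and are not estimates. The illustration fits outcomes expressed as risks. No mechanism or direction has been established separately for HIV incidence, uptake or stigma. The primary analysis and the school tuberculin outcome are untouched, and the planned HH contrast is much less exposed because ECF is balanced across it. This is an inexpensive improvement to the plan and does not threaten the trial's main conclusions.

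**What to change.** In the Analytic plan, add for household-cohort outcomes that HH v no HH (12 v 12, with ECF balanced) is the causal comparison. State that ECF v no ECF and arm 4 v arm 1 are descriptive and subject to selection through case detection, unless recruitment in a community closed before ECF began there. Judge ECF on the prevalence survey and the school tuberculin cohort.

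The cost is wording only: no change to recruitment, data collection or the HH estimate. The downside is that no causal claim is made for ECF, or for ECF plus HH, on household outcomes.
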